### Statistical analysis

All analyses will follow CONSORT guidelines. We will use standard descriptive statistics to compare basic sociodemographic and clinical data across treatment arms. We will use multilevel mixed models to investigate changes in cognitive and other scale scores over time. Mixed models provide estimates that are “intention-to-treat’ and allow for the investigation of interactions between group and time effects, as well as for the adjustment of possible imbalances between the groups following the randomisation. We will use imputed chain equations if the loss to follow up exceeds 25%. All probability tests will be two-tailed.

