#### Primary outcome measures

*Global cognitive abilities:* Due to hearing impairment, older people may experience difficulty in following verbal instructions or completing tasks that heavily rely on hearing during cognitive assessments. This may result in overestimation of cognitive impairment in such individuals [5]. Hence, we have used a non-verbal global cognitive measure that has been validated to use with the hearing impaired older adults. The global cognitive abilities will be measured using the Montreal Cognitive Assessment for the Hearing Impaired (HI- MoCA [11]. No significant difference was observed for MOCA and HI-MOCA scores in cognitively intact normal hearing participants, and the test-retest reliability coefficient was 0.66 [11].

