### Pilot test and sample size

In preparation of this trial, we conducted a pilot observational intervention study of two groups of hearing-impaired older adults: Group 1 [*n* = 35, mean age = 70.2 + 6.7 years, better ear four frequency average .5, 1, 2 & 4 kHz (BE 4PTA) = 31.92 dB, better ear high frequency average of 6 & 8 kHz (BE HF2PA) = 54.07 dB] and Group 2 [*n* = 13, mean age = 71.8 + 7.4 years, BE 4PTA = 33.46 dB, BE 2HFPTA = 55.57 dB]. A control group of 19 normal-hearing participants was also included. All participants completed hearing and a non-verbal cognitive assessment using the CANTAB test battery at baseline, 6 and 12 months. Hearing aids (HA) were fitted to Group 2 participants after the baseline assessment. Analysis of variance revealed that Group 2 participants (HA users) performed significantly better than Group 1 (non-HA users) on the delayed matching-to-sample (DMS) test of the CANTAB battery (*p* = .02, d = 0.38). We used G*Power software [34] to determine the required sample size for the study. Based on these pilot data, we calculated that a total of 140 participants would be required (70 in each group) to detect a conservative effect size of the intervention of d = 0.27 with two-sided α set at .05 and power of .90. To account for 25% of attrition over time, we estimated that a total of 180 participants would need to be recruited.

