### Randomisation, concealment and blinding

The computer-generated randomisation sequence will be stratified by the severity of the hearing loss (mild to moderate vs severe) based on the results of the hearing assessment. Each stratification block will be associated with a random sequence of numbers assigned to the intervention and control group in random permuted blocks of 6, 8 or 10. This sequence will be stored in a password-protected server housed at the University of Western Australia and will be managed by a biostatistician not involved in this project. Once a participant consents and is enrolled, s/he will be automatically ascribed a number and group membership (intervention or control).

Due to the nature of the intervention, participants will know their group assignment, but research staff involved in the assessment of cognitive function, quality of life, mood and physical function will remain blind to treatment allocation. This will be achieved by directing participants to **NOT**: (i) discuss any aspects of the intervention during the assessments, (ii) wear their HAs during the assessment. Binaural hearing amplifiers will be used to facilitate the communication between participants and research staff during all assessment visits (including the 12 and 24-month visits).

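### Covariate adjustment is justified only by chance imbalance, and the missing-data method switches at 25% observed loss, the trial's own planned attrition; one fixed primary model should replace both

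*Protocol article*

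**What the plan says.** In the protocol article, Statistical analysis, changes in cognitive and other scores are to be studied with multilevel mixed models. Among the merits listed for these models is that they permit group-by-time interactions, "as well as for the adjustment of possible imbalances between the groups following the randomisation". No other reason for covariate adjustment is given, and no covariate is named.

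The same section fixes a rule for missing data: "We will use imputed chain equations if the loss to follow up exceeds 25" per cent.

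Three other places bear on this:

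- Under Randomisation, concealment and blinding, the article says of allocation: "The computer-generated randomisation sequence will be stratified by the severity of the hearing loss (mild to moderate vs severe").
- Under Pilot test and sample size, it says of expected loss: "To account for 25% of attrition over time, we estimated that a total of 180 participants would need to be recruited".
- Procedures for the collection of study measures: assessments at baseline, 6, 12, 18 and 24 months, with the primary analysis at 12 months.

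**The concern.** Under sound randomisation, any difference between the arms at baseline arose by chance. Its size says nothing about how strongly a variable predicts the outcome, and prediction is what makes adjustment worthwhile. A plan that ties adjustment to imbalance can adjust for a weak covariate that happens to differ and pass over a strong one that happens to match. Two obvious candidates are known before the first participant is enrolled: baseline HI-MoCA and the hearing-loss stratum.

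The imputation rule makes the primary method depend on a quantity observed during the trial. Because the threshold equals the attrition that the design expects, nobody can say in advance which method will apply. At stake are a primary analysis that is not settled beforehand and precision that could be had without recruiting anyone.

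**Working it through.** **The plan's own figure.** The stated requirement is "a total of 140 participants would be required (70 in each group"), for d = 0.27 at a two-sided 5% level and 90% power. For two independent groups, n per arm = 2(1.960 + 1.282)² / 0.27² = 289, or 290 by the exact t calculation. With 70 per arm, power is 36%. The 140 is therefore not reproduced as a two-group comparison at d = 0.27. Allowing for 25% loss, 140 / 0.75 = 187, whereas 180 × 0.75 = 135. Both are separate points. They matter here only because they show that the trial has little power to spare.

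**How often the trigger fires.** With 180 randomised, 25% is 45, so the rule applies when 46 or more are lost. From the binomial distribution, P(X ≥ 46):

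| True loss | Probability that imputation is triggered |
|---|---|
| 20% | 4% |
| 25% (planned) | 46% |
| 30% | 92% |

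The article does not say at which visit loss is counted. Loss could be under 25% at 12 months, where the primary analysis sits, and over it by 24 months.

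**What the switch achieves.** A likelihood-based mixed model and chained equations, in their standard forms, both assume data missing at random. Loss of 24% or 26% does not change whether that assumption holds.

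**What planned baseline adjustment is worth.** The baseline to 12-month correlation r of HI-MoCA is not given. The nearest figure is in Primary outcome measures, where "the test-retest reliability coefficient was 0.66". That is only a proxy, so I use a range of 0.5 to 0.8. I take equal variances at the two visits, use baseline and 12 months only, and read d = 0.27 in SDs of the 12-month score. Relative variances V of the treatment contrast are:

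- unconstrained change from baseline: V = 2(1 − r)
- baseline as covariate: V = 1 − r²

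The ratio is (1 − r²) / [2(1 − r)] = (1 + r)/2, so baseline adjustment saves a fraction (1 − r)/2 of the sample. Power at 70 per arm is Φ(0.27 × √(70/2) / √V − 1.960), with 0.27 × √35 = 1.597.

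| r (assumed) | V, change | V, adjusted | Sample saved | Power, change | Power, adjusted | n per arm for 90% power, change / adjusted |
|---|---|---|---|---|---|---|
| 0.5 | 1.000 | 0.750 | 25% | 36% | 45% | 289 / 217 |
| 0.66 | 0.680 | 0.564 | 17% | 49% | 57% | 197 / 163 |
| 0.8 | 0.400 | 0.360 | 10% | 71% | 76% | 116 / 104 |

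**Adjusting only when imbalance is seen.** The article gives no criterion. As an illustration, suppose baseline is adjusted for only when its difference has p < 0.05, and otherwise the 12-month score alone is compared. Simulation (70 per arm, r = 0.66, 40,000 runs) gives a type I error of 0.038, against 0.050 when baseline is always adjusted for. This particular rule is conservative.

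**The case against.** The strongest reply is that this is one paragraph of a journal article and that the analysis plan is not shown. Much of that stands.

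- **A reader might infer that baseline HI-MoCA and the stratum are left out of the model.** The article does not support this. Baseline is an assessment visit, and a mixed model of change uses it in some form. Whether it enters as response or covariate is not stated, and a model with baseline means constrained equal would fit the text. Silence on the stratum is not proof of omission. If it were omitted, the test would be conservative: type I error is about 0.047, 0.043 or 0.039 for a stratum assumed to explain 2%, 5% or 10% of the variance.
- **A reader might infer a formal rule for selecting covariates by imbalance.** The sentence describes what mixed models make possible. It is a stated rationale, not a rule.
- **A reader might infer freedom to choose the analysis by its result.** Type I error would reach 0.069 if the smaller p-value of the change and adjusted analyses were taken, and 0.100 with the 12-month score as a third option. Nothing in the article permits that. The 25% rule is set in advance and depends on attrition, not on outcomes.
- **The 46% assumes true loss of 25% at the visit counted.** The article plans that loss over time in a 24-month study, so loss at 12 months may be lower. At 20% the probability is 4%.
- **Imputation with auxiliary variables can improve on a mixed model of the outcome alone.** This is correct, but the benefit comes from the auxiliaries and does not begin at 25%. It argues for running imputation in every case.

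Two stated choices remain: imbalance as the only reason given for adjustment, and a firm attrition threshold for the missing-data method.

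**Conclusion.** The point holds for those two choices. Selecting covariates by imbalance is inferior to naming them in advance for prognostic value. The 25% trigger leaves the primary missing-data method unsettled at the trial's own planned attrition, and it corrects nothing by switching. No inflation of false positives is shown.

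The gain from fixing baseline adjustment, measured against an unconstrained change analysis, is modest but real: 10% to 25% fewer participants, or about 5 to 10 percentage points of power at 70 per arm and d = 0.27. It rests on an assumed r of 0.8 down to 0.5, equal variances and a two-visit approximation. If the analysis already intends baseline as a covariate or constrained baseline means, this gain is already in hand and only the wording needs to change. The trigger should go in either case.

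**What to change.** State one primary model: a likelihood-based mixed model for HI-MoCA with group by categorical visit, baseline HI-MoCA as covariate (or baseline means constrained equal between arms) and the hearing-loss stratum as a fixed effect. Remove observed imbalance as a reason for adjustment.

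Delete the 25% trigger and use this model for all randomised participants whatever the attrition. Run chained-equation imputation in every case as a sensitivity analysis, with auxiliary variables such as CANTAB, mood and hearing-aid use.

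The cost is wording, a little programming and about two degrees of freedom. No extra participants or visits are needed.

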## Discussion

The current paper discusses the methodology for a randomised control trial that investigates whether hearing loss intervention using hearing aids could delay or arrest the cognitive decline in older adults with mild cognitive impairment. One of the strengths of this trial is that it follows CONSORT guidelines for the design of randomised controlled trials. The recruitment of participants with mild cognitive deficits was guided by our desire to test a population at risk of dementia (when prevention may be possible) and by the difficulties associated with the consenting of older adults with moderate to severe cognitive impairment. Besides, those with severe to profound hearing loss who meet the criteria for a cochlear implant will not benefit from HA amplification, hence, including them would potentially undermine the impact of HA amplification on cognitive functions, mental health and QoL. We acknowledge, however, that our study will focus on the cognitive decline rather than conversion to dementia. At this stage, this is a “proof of concept’ investigation, as a dementia prevention trial would require a substantially larger sample and follow up. The projected outcomes of the current study can immediately be translated to practice through audiology clinics and will be applicable across practices around the world. Findings can also be used to inform audiologists, general practitioners and other health-care providers. This will provide important information for older people about the use of hearing aids to prevent worsening cognitive impairment. In addition, consumer support will be requested in disseminating lay summaries/information to the community. If cognitive decline can be delayed or arrested, this would improve the quality of life of older adults who are at risk of developing dementia. It may also lower costs to the health-care and social support systems, by decreasing the needs for services and residential care placement. It would also significantly reduce the overall burden borne by the community.

## Data Availability

Not applicable.

## Abbreviations

ARHL: Age-related hearing loss
HA: Hearing aids
ESIA: Ear Science Institute Australia
HI-MOCA: Montreal Cognitive Assessment for the Hearing Impaired
3FAHL: Three Frequency Average Hearing Loss
HFAHL: High Frequency Average Hearing Loss
IADL: Instrumental Activities of Daily Living
dBHL: Decibel Hearing Loss
MOT: Motor Screening Task
CANTAB: Cambridge Neuropsychological Test Battery
AST: Attention Switching task
DMS: Delayed Matching Sample
PAL: Paired Associates Learning
SWM: Spatial Working Memory
SF-12: Health status and Quality of life: Short Form Survey
FCI: Functional Comorbidity Index
PHQ-9: Patient Health Questionnaire
GAI: Geriatric Anxiety Inventory
HHIE: Hearing Handicap Inventory of the Elderly
IOI-HA: International Outcome Inventory for HAs
CNC: Consonant-Nucleus-Consonant
CUNY: City University of New York
DDT: Dichotic Digits Test
SSI-ICM: Synthetic Sentence Identification with Ipsilateral Competing Message
Quick-SIN: Quick Speech in Noise
QoL: Quality of Life
COSI: Client Oriented Scale of Improvement
REIG: Real Ear Insertion Gain
CONSORT: Consolidated Standards of Reporting Trials
QALY: Quality Adjusted Life Year
